### Analysis

Planned intention-to-treat comparisons of the two groups at one week, six weeks and six months post-intervention (i.e. six months after t2 for both groups) will be conducted, with the primary dependent variable being mean daily walking, as assessed by pedometer. Mixed effects linear models will be fitted to compare the groups with a random practice effect to allow for clustering. The models will adjust for baseline characteristics at both practice and individual level. The former will include practice size and deprivation index, and the latter will include age, gender, BMI, ethnicity, employment status, educational level and clinical condition leading to referral.

As indicated above, the primary response will be the mean daily walking distance observed over up to seven days. Where less than five minutes walking is recorded for any particular day, the reading for that day will be treated as missing, and not used in calculating mean daily duration of walking. When individual days' data are missing, so long as data are available for two or more days, the mean will be taken over these non-missing days. If no data, or data from fewer than two days, are available for a particular patient at a particular timepoint, that assessment of walking will be treated as missing. These missing values will be imputed based on the baseline characteristics of the practice and individual [34]. A secondary analyses will be conducted excluding patients with missing data.

Planned exploratory sub-group analyses will be conducted to determine if the intervention has larger or smaller effects for groups defined in terms of age, ethnicity, gender, socio-economic status, or clinical condition, to provide information on any adverse impacts on social inequality.

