A 2006 review from the National Institute of Health and Clinical Excellence (NICE) concluded that, although there is considerable evidence for the benefits that accrue from walking, there is a shortage of effective interventions that can be offered to patients in primary care [7]. This conclusion was unchanged when the review was updated in 2011. The advantages of a primary care setting are that this is where most of the population has regular contact with the healthcare system, and often in circumstances where they are receptive to advice to alter their behaviour. There has also been increased delivery of lifestyle advice by practice nurses (PNs) and healthcare assistants (HCAs), based in, or working closely with primary care. If an intervention to increase walking in primary care is effective and cost-effective, then primary care offers the possibilities of scaling this up to allow a large proportion of the population to receive the benefits of being more physically active.

The present study protocol describes a cluster randomised controlled trial of an intervention to increase walking in primary care which was designed to address the lack of effective interventions that can be offered to patients identified by NICE. In line with the Medical Research Council (MRC) framework for development and evaluation of complex interventions [8,9], the trial intervention and procedures build on previous formative research [10-14], based on explicit theory [15-17].

Extended developmental work was conducted using the Theory of Planned Behaviour (TPB), a social cognition model which can be used to predict and explain any behaviour in terms of a limited set of constructs [15]. A review of previous research using this theory identified perceived behavioural control (PBC) as the strongest predictor of intentions to walk more [13]. According to the TPB, PBC is underpinned by control beliefs: beliefs about which factors make it easy or difficult to perform the behaviour [15]. The most common control beliefs regarding walking in a general public sample [10] were identified as related to lack of time, indicating that the intervention should aim to address these beliefs. As PBC is a highly similar, if not identical, construct to self-efficacy [18], the literature on altering self-efficacy was consulted [16], which suggested that mastery experience was likely to be effective [16].

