### Outcome measures

The main outcome measure will be mean daily number of minutes walked in the past week, assessed at all time points using the New Lifestyles NL-1000 Activity Monitor Pedometer (New-Lifestyles Inc, Lees Summit, Missouri, USA). This pedometer provides readings on number of minutes walked and step counts, over each of the previous seven days. The intensity threshold of each pedometer will be set to record movement on a setting of four or above (the range is 1 to 9), to assess physical activity of at least moderate intensity.

Psychological process will be assessed using one of two Theory of Planned Behaviour (TPB) [15] questionnaires, both of which measure several constructs. A longer 26-item version measures intentions, self efficacy/ PBC, attitudes, subjective norms, control beliefs and associated perceived power to inhibit/ facilitate behaviour in relation to walking for at least 30 minutes on average a day over the next 7 days [29]. A brief 6-item version of the questionnaire assesses only intentions, self efficacy/ PBC, attitudes, and subjective norms. Both versions of the TPB questionnaire are abbreviated versions of measures previously developed [10] and validated [13,14] in studies of walking with an adult volunteer general public sample.

Data on NHS resource use and personal costs to patients will be collected using standard measures for economic analysis [30]. Impact on Quality of Life will also be assessed using the EQ-5D questionnaire [31,32]. Comparing this with costs (directly and indirectly related to patient management) will enable incremental cost-effectiveness of the intervention to be estimated.

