#### Patient consent, receipt of intervention, and follow-up measurements

For both experimental conditions, each patient attends a face-to-face session at their own practice with the PN/HCA who is delivering the session. During this session, they are screened for whether they already do more than 30 minutes of moderate or vigorous physical activity per day on at least 5 days a week. If they are not already achieving this recommended level of physical activity, they are asked to provide informed consent, and complete the baseline (t1) questionnaire, which includes the full TPB measure, the EQ5D, and measures of ethnicity, employment status and education level. Information on patient date of birth, gender, and the clinical condition for which they were flagged (e.g. diabetes, hypertension, etc) will be recorded on a standardised form by PN/HCAs. The form will be sent to the research team, along with their contact details. Weight and height information for each patient will be recorded by the PN/HCA at baseline, which will allow calculation of body mass index. After this point, the procedure differs for patients in practices allocated to the self-regulation intervention condition, and patients in practices allocated to the information provision condition (see Figure 1).

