**Figure 1 F1:**
[figure not shown]
**Flowchart showing planned study recruitment numbers, and timing of intervention sessions and measurements**.

For patients in practices allocated to the information provision control condition, the session will continue with delivery of the "information provision" intervention as described above: the PN/HCA will provide their patients with an information pack of materials promoting walking, and answer any questions the patient may have about walking more. At the end of this session, patients complete the post-intervention (t2) questionnaire, consisting of the brief TPB measure only, and are given a pedometer, with detailed instructions in its use. They are asked to wear it for a week, and return to the research team in a reply-paid envelope. This forms the first post-intervention assessment of walking.

For patients in practices allocated to the self-regulation intervention condition, the PN/HCA provides their patients with an information pack of materials promoting walking, and answers any questions the patient may have about walking more. Following this, two further face-to-face appointments will be booked, for delivery of the self-regulation intervention (as described above), at one week and two weeks after this initial session, plus the final intervention session four weeks after the initial session. At the end of this session, patients are given a pedometer, with detailed instructions for its use. They are asked to wear it for a week, and return it at their first intervention session where the PN/HCA will extract the data from the pedometer. This initial assessment of walking constitutes a pre-intervention measurement for those patients in the intervention arm.

Patients in practices allocated to the intervention condition then receive the self-regulation intervention, as detailed above. Sessions one and two will be tape-recorded, with the explicit agreement and signed consent of the patients involved. At the end of the second face-to-face session, patients complete the post-intervention (t2) questionnaire, and are given a pedometer, to wear for a week, and then return to the research team in a reply-paid envelope. This forms the first post-intervention assessment of walking.

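### The walking models adjust for no walking-related baseline, although both arms complete the TPB questionnaire at t1; adding its scores is a cheap improvement, not the repair of an error

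*Protocol article*

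**What the plan says.** The Analysis section plans mixed linear models with a random practice effect at one week, six weeks and six months. At practice level, "The former will include practice size and deprivation index". At individual level, "the latter will include age, gender, BMI, ethnicity, employment status, educational level and clinical condition leading to referral". Missing walking values are to be imputed from baseline characteristics of practice and patient, which are not listed further.

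Under Patient consent, receipt of intervention, and follow-up measurements, patients in both arms "complete the baseline (t1) questionnaire, which includes the full TPB measure, the EQ5D, and measures of ethnicity, employment status and education level". The same section then says "After this point, the procedure differs for patients in practices allocated to the self-regulation intervention condition", so t1 comes before the arms diverge. According to Outcome measures, the longer TPB version "measures intentions, self efficacy/ PBC, attitudes, subjective norms, control beliefs and associated perceived power to inhibit/ facilitate behaviour in relation to walking".

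The pedometer schedule differs by arm. In the text accompanying Figure 1, intervention patients wear a pedometer for a week before their first intervention session: "This initial assessment of walking constitutes a pre-intervention measurement for those patients in the intervention arm". Control patients receive their first pedometer after the information session, and that week is their first outcome.

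The only analysis that uses the t1 TPB scores is the Process evaluation, where they are the starting point of change scores for mediation.

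**The concern.** The protocol's own theory treats self-efficacy/PBC and intention as determinants of walking. Their baseline values are available in both arms, yet the main comparison does not use them. No pedometer baseline can take their place, since the control arm has none.

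Two things are at stake. The first is precision, if the scores predict later walking. The second matters more. Under Practice recruitment and Practice randomisation, a practice is allocated once it and its PN/HCA have agreed. Patients are screened and give consent later, at a session with a PN/HCA who knows the arm. Randomising practices does not by itself keep the motivation of entrants equal in that sequence, and 20 clusters leave room for chance differences. None of the listed covariates measures motivation to walk, so an imbalance in it would largely pass into the estimated effect.

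**Working it through.** **Inputs from the Sample size section.** 400 patients; 20 PN/HCAs, 10 per arm, 20 patients each; SD 15 min/day; ICC 0.010; target difference 5 min/day; stated power 85%.

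**Assumptions.** Two-sided alpha of 0.05 (not stated in the article). Partial correlation r between the t1 TPB score and later walking, given the covariates already listed, of 0.1 to 0.3. The documents give no value for r. The Background calls the link between intention and walking low, so a low range is used.

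**Step 1: the plan's own figure.**
- Design effect = 1 + (20 − 1) × 0.010 = 1.19.
- Effective n per arm = 200 / 1.19 = 168.1.
- SE = 15 × √(2 / 168.1) = 1.636 min/day.
- Power = Φ(5 / 1.636 − 1.96) = 86.3%.

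This is within two points of the stated 85%, with no covariate gain assumed. A t reference with 18 degrees of freedom gives 82.4%; that gap comes from the small number of clusters, not from the covariate list.

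**Step 2: precision with t1 TPB added.** Residual SD = 15 × √(1 − r²), and the SE shrinks by the same factor.

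| r | Residual SD | SE | Fall in SE | Power | Gain (points) |
|---|---|---|---|---|---|
| none | 15.00 | 1.636 | – | 86.3% | – |
| 0.1 | 14.92 | 1.628 | 0.5% | 86.7% | 0.3 |
| 0.2 | 14.70 | 1.603 | 2.0% | 87.7% | 1.3 |
| 0.3 | 14.31 | 1.561 | 4.6% | 89.3% | 3.0 |

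**Step 3: bias from imbalance.** Shift = imbalance in SD units × r × 15. For a hypothetical 0.2 SD difference between arms at t1:
- r = 0.1: 0.2 × 0.1 × 15 = 0.3 min/day (6% of the 5 min/day target)
- r = 0.2: 0.6 min/day (12%)
- r = 0.3: 0.9 min/day (18%)

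Using the full SD of 15 with a partial r slightly overstates these shifts.

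**Step 4: how likely is 0.2 SD?** If the TPB score has the same ICC as walking, the chance imbalance has SE √(2 / 168.1) = 0.109 SD. A difference of 0.2 SD is then 0.2 / 0.109 = 1.83 SEs, which arises by chance about 7% of the time in either direction. Differential recruitment could add to it, but the documents give no figure for that.

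**The case against.** The case for leaving the plan alone is substantial, and much of it stands.

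- **Nothing is misstated.** The model already has both stratification factors and seven individual covariates. Its wording need not be exhaustive, and an SAP could add terms. A reader might infer that the plan contradicts itself or is defective here; it does not and is not.
- **Evidence for prognosis is thin.** A reader might take the Background as showing that baseline self-efficacy strongly predicts walking. It says that an earlier review "identified perceived behavioural control (PBC) as the strongest predictor of intentions to walk more", which concerns intentions, not walking. The earlier trial's self-efficacy result concerns changes as mediators, not baseline scores as predictors. Correlations of 0.4 or 0.5 would give 91.5% or 94.2% power, but nothing in the documents supports them.
- **Self-efficacy and intention are not the only walking-related baseline.** The same questionnaire also covers attitudes, norms and control beliefs. At the first session in both arms, "they are screened for whether they already do more than 30 minutes of moderate or vigorous physical activity per day". That screen is an eligibility condition which all entrants pass on the same side, so it is of little use as a covariate. What stands is that the TPB questionnaire is the only graded walking-related instrument completed in both arms before procedures diverge.
- **The adjustment is not perfectly neutral.** The t1 answers are given after allocation, to a PN/HCA who knows the arm. The longer TPB items also ask about the next seven days. For controls that is the first outcome week; for intervention patients it is the pre-intervention pedometer week. The scores may therefore predict the one-week outcome differently by arm. These are small drawbacks, and a sensitivity analysis would show whether they matter.
- **Imputation.** The planned wording does not exclude the TPB scores. It does not secure them either.

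**Conclusion.** The point holds as a modest recommendation. The walking models use no walking-related baseline, while a suitable instrument is already completed in both arms and the pedometer baseline exists in one arm only.

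A reader might infer that the trial is underpowered without this adjustment. It is not: the stated 85% was reached with no covariate gain. The likely benefit in precision is about 0.5% to 5% of the SE and 0.3 to 3 power points. The better reason to act is partial protection against unequal motivation at entry, worth about 0.3 to 0.9 min/day for a hypothetical 0.2 SD imbalance. Both ranges rest on an assumed partial r of 0.1 to 0.3, and the 0.2 SD is illustrative, not observed.

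Nor would the adjustment remove selection at recruitment or replace a two-arm pedometer baseline. Those are separate and larger weaknesses of the design.

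**What to change.** In the Analysis section:

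1. Add t1 self-efficacy/PBC and t1 intention to the prespecified individual-level covariates at one week, six weeks and six months.
2. Name the same two scores among the predictors in the imputation model for missing walking. Postal return of a pedometer plausibly depends on motivation.
3. Report the model without them as a sensitivity analysis, because t1 is answered after practice allocation.

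The cost is two model terms and one extra reported analysis, with no new data collection. The terms should be fixed before outcome data are seen, since adding them later would look selective.

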#### Patients

To be eligible for inclusion in the trial, potential participants must be patients in a participating practice, as well as:

a) be aged between 16 and 65 years old,

b) have one of the following chronic conditions where physical activity has been shown to have a positive effect on health status [1]: hypertension, type 2 diabetes, pre-diabetes (impaired glucose tolerance, insulin resistance), low back pain, fibromyalgia, coronary heart disease, cardio-vascular disease, hypercholesterolemia, osteoporosis and osteoarthritis, or are overweight or obese,

c) not currently being investigated/treated by secondary care specialists for the condition (s) or are awaiting investigation/treatment by secondary care specialists for the condition (s),

d) are "sedentary" in terms of not meeting the 30 mins/day at least 5 times/ week guidelines [1],

e) are able to speak English (and therefore could potentially benefit from the PN/ HCA intervention session). This is because the intervention is to be delivered and interpreted verbally and there are not sufficient resources to employ interpreters. Where participants cannot adequately read English, the PN/HCA will read the patient information sheet, consent form and worksheet instructions.

f) do not have learning difficulties that would preclude active engagement with the intervention session,

g) do not have mental health problems i.e. anxiety, depression that would preclude active engagement with the intervention session, or where the patient is being investigated/treated by secondary care specialists for the problem,

h) wish to participate,

i) receive a letter of invitation to the study from their practice.

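### Treating every day under five recorded minutes as missing confuses non-wear with inactivity and changes the primary outcome, with bias of unknown size and direction

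*Protocol article*

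**What the plan says.** The Outcome measures section defines the primary outcome: "The main outcome measure will be mean daily number of minutes walked in the past week". On the device it adds: "This pedometer provides readings on number of minutes walked and step counts, over each of the previous seven days". It also says: "The intensity threshold of each pedometer will be set to record movement on a setting of four or above", so that only activity of at least moderate intensity is counted. Eligibility (Patients section) requires patients to be sedentary, "in terms of not meeting the 30 mins/day at least 5 times/ week guidelines".

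The Analysis section then turns daily readings into a score in three steps:

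- Day level: "Where less than five minutes walking is recorded for any particular day, the reading for that day will be treated as missing". The rule has no exception and no wear condition.
- Patient level: "so long as data are available for two or more days, the mean will be taken over these non-missing days".
- Otherwise: "If no data, or data from fewer than two days, are available for a particular patient at a particular timepoint", the assessment is missing. "These missing values will be imputed based on the baseline characteristics of the practice and individual".

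The one alternative analysis that the article states leaves out patients with missing data; it does not alter the day rule.

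**The concern.** A reading of 0 to 4 minutes can mean that the device was not worn, or that it was worn on a day with almost no brisk movement. The second is a valid value of the outcome, and it is plausible in sedentary patients with a threshold set at moderate intensity. The rule treats both alike.

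Two things follow. First, the score averages over days selected by their own outcome value after randomisation, so it is a different quantity from the one defined in Outcome measures. Second, a patient with only one day, or none, of at least five minutes becomes missing because of low walking. If the arms differ in walking, they will tend to differ in how many days and patients are removed.

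Imputing from baseline characteristics does not undo this. The missingness depends on the walking itself, and a pre-intervention pedometer reading is described only for the intervention arm. The same score also feeds the cost-effectiveness ratio in the Economic evaluation section.

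**Working it through.** **1. The plan's own figure.** Inputs from Sample size: 200 patients per arm in clusters of 20, SD 15, ICC 0.010, difference 5 min/day. Two-sided alpha of 0.05 is assumed, since none is stated.

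- Design effect = 1 + (20 − 1) × 0.010 = 1.19.
- Effective n per arm = 200/1.19 = 168.1.
- SE = 15 × √(2/168.1) = 1.64, and 5/1.64 = 3.06.
- Power = Φ(3.06 − 1.96) ≈ 86%, against the stated 85%.

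The power statement reproduces. It applies to a 5 min/day difference on the outcome as defined.

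**2. What the rule estimates.** Let p be the share of days with at least five minutes and m the mean on those days. Take the other days as 0 for simplicity.

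- True mean = p × m. Score under the rule = m.
- True arm difference = p_T m_T − p_C m_C. Recorded difference = m_T − m_C.
- If only p changes, the recorded difference is 0.
- If only m changes and p is equal in both arms, the recorded difference is the true one divided by p, so it is inflated.

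**3. Worked cases over seven worn days.**

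| Comparison | True means | True difference | Scores under the rule | Recorded difference |
|---|---|---|---|---|
| 30 min on 2 days v 5 days, else 0 | 60/7 = 8.6 v 150/7 = 21.4 | 12.9 | 30 v 30 | 0 |
| 20 min on 4 days v 6 days, else 0 | 80/7 = 11.4 v 120/7 = 17.1 | 5.7 | 20 v 20 | 0 |
| 3 days at 0 in both arms; 4 days at 20 v 28.75 | 80/7 = 11.4 v 115/7 = 16.4 | 5.0 | 20 v 28.75 | 8.75 |
| 30 min on 2 days; the other 5 days at 0 v 10 | 60/7 = 8.6 v 110/7 = 15.7 | 7.1 | 30 v 15.7 | −14.3 |

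A patient with 30 minutes on one day only has a true mean of 30/7 = 4.3. The rule gives no score, and an imputed value takes its place.

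**4. Simulation under assumed daily patterns.** There were 200,000 patients per arm, seven days each and no non-wear. Person means and day-to-day variation were gamma (coefficients of variation 0.7 and 0.6), with or without an extra class of days at 0 to 5 minutes. Patients with fewer than two qualifying days were left out, so imputation is not modelled. None of these inputs is in the protocol. The true difference was about 5 min/day throughout. The control mean was 15, except in the two rows without inactive days, where it was 10 to 20.

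| How the gain arises | Recorded difference |
|---|---|
| Inactive days become active | about −0.4 |
| About half from such days | 2.1 to 3.2 |
| Proportional, no separate inactive days | 4.4 to 4.6 |
| +5 on every day, no separate inactive days | 1.7 to 2.8 |
| +5 on every day, 10–40% of control days inactive | 1.0 down to −5.9 |
| Only active days lengthen, inactive share fixed | 5.1 to 7.9 |

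At a control mean of 15 the rule reported 17.6 to 25.9. It removed 25% to 49% of control days and set 9% to 20% of control patients to missing, against 0% to 17% in the intervention arm.

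**The case against.** The best defence is that the rule stands in for non-wear. Pedometers are worn unsupervised and mostly returned by post, so unworn days will occur, and scoring them as zero would also bias the outcome. A record of 30 minutes on five days and 0 on two has a worn-day mean of 30 if the two days were unworn, and 21.4 if they were worn. The rule is right in the first case and wrong in the second. That stands as a reason to have a wear rule. It does not support one that cannot tell the two cases apart. The simulations contain no non-wear, so they show the rule's cost and not its benefit.

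It is also fair that the eligibility criterion does not imply many days under five minutes. A patient walking 25 minutes every day qualifies, and the rule leaves that patient's score unchanged. How often worn days fall below five minutes is unknown.

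A reader might infer that the bias runs mainly towards zero, since most of the simulated patterns attenuate the difference. The documents do not support that. The patterns were chosen, so counting them gives no probability, and lengthening active days alone inflates the difference. Nor does the protocol say that the intervention targets days without walking: it describes recalling successful long walks, setting goals and making action plans, which could yield longer walks, more walking days or both.

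Finally, the full protocol and analysis plan are not shown, so the absence of a further sensitivity analysis from the article is not held against it. The objection is to the rule the article states.

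**Conclusion.** The concern holds, and the rule should be changed before the data are analysed. By the text alone, the analysed score is mean minutes on days of at least five minutes. That differs from the defined primary outcome whenever a worn day falls below the cut-off. The missingness it creates depends on the outcome, and the stated imputation and complete-case analysis do not remove it.

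Size and direction are not fixed by the documents. They depend on how often worn days read under five minutes and on whether the gain comes from more walking days, longer ones or a proportional rise. For a true difference of about 5 min/day, the assumed patterns gave anything from a reversed sign to 7.9. A specific loss of power should not be inferred: at SD 15 a recorded difference of 4, 3 or 2.5 min/day would have 69%, 45% or 33% power, but nothing in the protocol says which, if any, would occur.

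**What to change.** - Define a non-worn day from the daily step count (for example zero or near-zero steps), with the cut-off fixed in advance and blind to arm.
- Score every worn day at its recorded minutes, including readings of 0 to 4.
- Apply the two-day minimum to worn days.
- Keep the five-minute rule as a sensitivity analysis.

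The cost is a change of analysis wording and the choice of a cut-off; the device already stores the step counts, so no new data are needed. The drawback is that steps come from the same device and are an imperfect sign of wear. Some very low-step or partly worn days may be misclassified, so a second cut-off should be run as a sensitivity analysis.

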Patients in practices allocated to the intervention condition receive a final follow-up intervention session, which may be by telephone or face-to-face, two weeks after their second face-to-face session. Despite this, the measurement procedures for patients in practices in both conditions are identical from t2 onwards.

At six weeks post intervention (i.e. six weeks after t2 for both groups), all patients are sent a questionnaire by post (t3) containing the brief TPB measure, and a pedometer, and asked to return these by post. At six months post intervention (t4), all patients are sent a questionnaire containing a full TPB measure, the EQ5D, and a final pedometer, which again they are asked to return by post.

To encourage retention, all participants who complete and return questionnaires or pedometers from t2 onwards will be sent postal feedback on their walking behaviour and psychological measurements in the form of a postal profile. Those who do not send back the pedometer at any measurement point will receive a reminder letter and follow-up telephone calls from the research team encouraging them to return these, as loss of numerous pedometers will be expensive, and threaten the validity of the study.

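### Missing walking outcomes are to be imputed from baseline characteristics that do not include trial arm; followed as written, this pulls the primary intention-to-treat estimate towards zero

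*Protocol article*

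**What the plan says.** All of the following is in the Analysis section of the protocol article unless another section is named.

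- The main comparison: "Planned intention-to-treat comparisons of the two groups at one week, six weeks and six months post-intervention". It uses mixed effects linear models that compare the groups, with a random practice effect and adjustment for baseline characteristics.
- Those characteristics are spelled out, first for the practice and then for the patient: "The former will include practice size and deprivation index, and the latter will include age, gender, BMI, ethnicity, employment status, educational level and clinical condition". Trial arm and walking readings are in neither list.
- An assessment counts as missing under this condition: "If no data, or data from fewer than two days, are available for a particular patient at a particular timepoint". Days with less than five recorded minutes have already been set to missing by then.
- The handling of such assessments: "These missing values will be imputed based on the baseline characteristics of the practice and individual". An imputation source is cited.
- The fallback: "A secondary analyses will be conducted excluding patients with missing data".

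The section on patient consent, receipt of intervention and follow-up measurements shows which other readings exist. After the intervention, "the measurement procedures for patients in practices in both conditions are identical from t2 onwards", so both arms have walking at one week, six weeks and six months. Before it, only one arm is measured: "This initial assessment of walking constitutes a pre-intervention measurement for those patients in the intervention arm". Baseline walking therefore cannot serve as a common predictor.

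**The concern.** The model that compares the groups contains arm. An imputation model without arm gives patients with the same covariates the same expected value whichever arm they are in. Each imputed patient then adds nothing to the expected arm difference, but still counts in the denominator of that patient's arm.

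The effect falls on the primary analysis and has a known direction. The analysis that excludes patients with missing data does not share this bias, but it ranks second. The article presents the trial as definitive and explanatory, so a diluted estimate could be read as an intervention that failed. The Economic evaluation section also uses mean daily minutes walked as an effect measure, so the dilution would carry into that cost-effectiveness ratio.

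**Working it through.** **Inputs from the Sample size section.** 20 practice nurses or healthcare assistants (10 per arm), 20 patients each, 400 patients in all; SD 15 min/day; ICC 0.010; difference 5 min/day; stated power 85%.

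**Assumed because not stated.** Two-sided alpha 0.05; missing fraction f.

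**Step 1: the plan's own figure.** Design effect = 1 + (20 - 1) × 0.010 = 1.19. Effective number per arm = 200 / 1.19 = 168.1. SE = 15 × √(2 / 168.1) = 1.636. Power = Φ(5 / 1.636 - 1.96) = Φ(1.096) = 86.3%. This agrees with the stated 85%, so the inputs are the right ones. A t test on 18 df gives 82.4%.

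**Step 2: expected estimate when arm is left out.** Let the true means be μ (control) and μ + δ (intervention), the missing fractions f0 and f1, and let p be the share of observed patients who are in the intervention arm. With balanced covariates and data missing completely at random, the imputation model predicts μ + pδ in both arms. The completed-data means are then:

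- intervention: (1 - f1)(μ + δ) + f1(μ + pδ)
- control: (1 - f0)μ + f0(μ + pδ)
- difference: δ × [(1 - f1) + (f1 - f0)p], with p = (1 - f1) / [(1 - f1) + (1 - f0)]

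When f1 = f0 = f this reduces to δ(1 - f). With δ = 5:

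| Assumed f, both arms | Expected estimate (min/day) |
|---|---|
| 5% | 5 × 0.95 = 4.75 |
| 10% | 5 × 0.90 = 4.5 |
| 20% | 5 × 0.80 = 4.0 |
| 30% | 5 × 0.70 = 3.5 |

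Unequal fractions also shrink the estimate. For 10% and 20%, p = 0.9 / 1.7 = 0.529 and the result is 5 × (0.9 - 0.1 × 0.529) = 4.24. For 10% and 30%, p = 0.9 / 1.6 = 0.5625 and the result is 5 × (0.9 - 0.2 × 0.5625) = 3.94.

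**Step 3: simulation.** 600 trials per cell, 10 imputations combined by Rubin's rules, cluster-level t test on 18 df, data missing completely at random. Assumed: covariates explain 10% of the variance, and the within-patient correlation with one other walking reading is 0.6. Each cell gives the mean estimate and the power. The Monte Carlo SE is about 0.05 to 0.08 for the estimate and about 2 percentage points for power.

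| Imputation model | 10% missing | 20% missing | 30% missing |
|---|---|---|---|
| Baseline, no arm | 4.44; 75.7% | 4.06; 63.8% | 3.57; 46.8% |
| Baseline + arm | 4.97; 82.2% | 4.97; 77.3% | 5.17; 75.3% |
| Baseline + other reading, no arm | 4.86; 80.7% | 4.63; 78.8% | 4.46; 72.3% |
| Baseline + arm + other reading | 5.05; 83.5% | 5.00; 80.5% | 5.02; 78.5% |
| Complete cases, no imputation | 4.93; 82.7% | 4.94; 77.2% | 5.08; 73.7% |

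The first row matches Step 2 within simulation error. The second row returns to about 5.0; its 5.17 lies a little over two Monte Carlo SEs above 5, which is unremarkable among 15 cells. The third row shows that another reading without arm removes only part of the shrinkage. The fourth row, set against the second, shows that once arm is present the other reading leaves the expected estimate unchanged; the power differences of about 1 to 3 points favour including it, but they are of the order of the simulation error.

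**The case against.** **The text does not say that nothing else enters the imputation.** The sentence is a one-line summary in a journal article and cites a source that is not shown; a full protocol or SAP may give more. It reuses the covariate phrase from the description of the comparison model, so it could be shorthand for that whole model, arm included. This stands as a limit: the document does not prove that arm will be left out. It does not remove the point, because the article names a predictor set, and that set gives a biased primary estimate.

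**Detail belongs in the SAP.** This is fair for the number of imputations and the choice of auxiliary variables. Their absence is not the complaint.

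**The size is conditional.** Also fair. No missing fraction is given, and the plan tries to limit loss through reminders, telephone calls, postal feedback and acceptance of two valid days. At 5% missing the estimate falls only to 4.75. On the other side, returns after the intervention are by post, days under five minutes are discarded in a sedentary population, and the Sample size section shows no allowance for attrition.

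**The complete-case analysis would reveal the problem.** Comparing the two could expose the attenuation, but it would not repair the primary estimate.

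**A stronger reading that a reader might infer** is that leaving out the patient's other walking readings causes the same proportional bias. The simulation does not support it: with arm included and data missing completely at random, the estimate stays at about 5.0 with or without the other reading. Nor does the article give any correlation between readings; the 0.6 used here is an assumption.

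**Conclusion.** The point holds and concerns the primary estimate. Followed as written, the imputation biases the arm difference towards zero, and the cause is the absence of arm alone. The size is about δ(1 - f), with a matching loss of power: roughly 6, 14 and 29 percentage points at an assumed 10, 20 and 30% missing (82.2 - 75.7, 77.3 - 63.8 and 75.3 - 46.8).

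Exact proportionality needs similar missing fractions in the two arms and an imputation without practice intercepts. Because arm is allocated by practice, such intercepts would carry part of the arm difference into the imputed values.

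Omitting the other walking readings is secondary: it loses precision and makes missing-at-random harder to defend.

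A reader might also infer that complete cases, or imputation with arm, are free of bias in general. That was shown only under missing completely at random. The rule that discards days under five minutes ties missingness to low walking, so neither is guaranteed.

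**What to change.** Replace the imputation sentence with one stating that missing walking outcomes will be multiply imputed from a model containing trial arm (or run separately by arm), all covariates of the analysis model and the practice effect. Preferably add walking at the other post-intervention time points (t2, t3, t4) as auxiliary predictors. If the intended model already contains arm, correct the sentence to say so.

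A repeated-measures mixed model fitted to all available readings, with arm-by-time, patient and practice effects, would be an acceptable alternative but is not a required correction.

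The cost is one sentence and a little programming. No new data are needed, and neither the design nor the sample size changes.
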